## 2. Materials and Methods

### 2.1. Study Design

TREMNIOS is a multicenter single-arm pilot clinical trial which will be performed in the Polish population of adult patients with MetS and eating period of ≥14 h per day. The essential components of the research plan and its timeline are depicted in Figure 1.

The study will consist of 1 week of screening, 2 weeks of baseline assessment, 12 weeks of monitored intervention, and 12 weeks of self-directed intervention. The participants will be asked to restrict their food intake to 10 h a day and fast for the remaining 14 h over 12 weeks of TRE monitored intervention. Eating (dietary timing and intake, and compliance with TRE), sleep, and physical activity patterns will be assessed throughout the study with a custom-made smartphone application (mCC app) [25]. During the TRE monitored intervention, participants will receive education and support, including daily prompts from the mCC app. Then, the participants will enter the 12-week self-directed TRE intervention during which they will continue the TRE intervention and use the mCC app to record all dietary intake, exercise, and sleep. During the self-directed intervention, participants will not receive feedback from study team members or the mCC app.

The primary study outcome that characterizes the feasibility of TRE intervention in population of patients with MetS is an adherence to TRE intervention that is defined as the proportion of total number of days recorded with mCC app during the TRE monitored intervention period in which participants satisfied a requirement of a 10-h TRE eating window. In addition to the adherence, other characteristics of the feasibility of the TRE program will be evaluated. These characteristics include screening failure rate (i.e., a number of persons screened compared to final enrollment), retention rate (i.e., a number of participants enrolled compared to the number of participants who finish the final study measures), reasons for screening failures and dropout from the study, as well as an adherence to mCC app (i.e., completion of mCCapp logs). The evaluation of this information will support the assessment of effectiveness of recruitment strategies and methods of monitoring adherence to TRE.

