### 2.5. TRE Intervention

At Visit 3 (Week 3—intervention begins), participants will return to remove the CGM and review their mCC app data. Participants who are eligible based on blood work results and logging mCC app data will be subject to further steps of the trial. The food intake data from the baseline period will be downloaded from the server-side of the mCC app and the review of the data will be performed. Participants who satisfy logging criteria (recording ≥3 meals or beverages daily for at least 5 days a week) and have an eating interval of ≥14 h a day will undergo further approach. Participants who record <2 meals/day for >3 days or those with <6.5 h self-reported sleep for >3 days based on their data from the mCC app will be excluded from the study. The participants who meet the criteria for MetS (based on blood work results, BP, and/or waist circumference measurements), the mCC app logging criteria, and the BDI-II and ESS questionnaire criteria will be enrolled in the study (Table 1).

At Visit 3, participants will enter a 12-week monitored intervention between Weeks 3 and 15. Participants will meet with a dietitian in-person for behavioral nutritional counseling. At this visit, participants will be asked to restrict their food intake daily to 10 h a day and fast for 14 h. They will also be instructed to start the TRE intervention by selecting (together with study investigator) a 10-h eating window that best suits their lifestyle based on his/her baseline eating pattern from the first 2 weeks. This 10-h window must be between 7 a.m. and 9 p.m., with the last meal (including non-water beverage) consumed at least 2 h prior to the typical bedtime. The 10-h interval will be entered in the app, so participants can visualize their chosen daily eating window and consume all meals within this interval. Beverages that include caffeine or artificial sweeteners are not allowed outside of the 10-h feeding period, as some artificial sweeteners may affect glucose tolerance and caffeine can alter metabolism. Participants will also be able to modify the 10-h window based on their schedule; however, eating outside of the eating window by more than one hour more than twice per week is not allowed. TRE will be the only intervention, and participants will not be instructed to change their habits regarding physical activity or the quality, quantity, or caloric content of their diet.

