During the 12-week monitored intervention, participants will continue to use the mCC app to document all dietary intake, exercise, and sleep quantity/quality. They will record their dietary intake by taking a picture of a food meal and/or beverage and/or annotating the food (with the food name, portion size, etc.). The mCC app will be programmed so that participants can visualize their caloric intake spread over the wakeful hours. Participants will receive push notifications (2–3 times a week) to provide information about TRE and metabolic health. The mCC app can be set by participants to alert them 30 min prior to the end of the eating interval to finish their last meal of the day. At Visit 4 (Week 13), which is 10 weeks into the intervention period, the participants will return to the clinic to have the CGM device placed for 2 weeks. At Visit 5 (Week 15), participants will visit the clinic to remove the CGM. At this visit, they will also have a fasting blood draw, vital signs assessment, body composition measurement, and be asked to complete the same general health and chrono-nutrition questionnaires as at Visit 1.

After 12 weeks of monitored intervention, participants will enter a 12-week self-directed intervention for up to a 6-month point. Beyond Week 15, participants will continue to use the mCC app to document all dietary intake, exercise, and sleep quantity/quality. During the 12-week self-directed intervention, no feedback from study investigators or push notifications from the mCC app will be provided to participants. At Visit 6 (Week 25), participants will return to the clinic for the application of CGM for 2 weeks. At Visit 7 (Week 27—intervention ends), participants will visit the clinic to remove the CGM. At this visit, they will also have a fasting blood draw, vital signs assessment, body composition measurement, and be asked to complete the same general health and chrono-nutrition questionnaires as at Visit 1.

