#### 2.6.4. myCircadianClock Application

The mCC app is a free smartphone application that was developed at the Salk Institute for Biological Studies, La Jolla, CA 92037, USA [25]. [name] and [name] from the Salk Institute, who are also members of the research team of this study, are the administrators of data collected on the server using this application.

The mCC app will serve as an electronic food, activity, and sleep diary. During the TRE intervention, data from the mCC app will be used to assess participant adherence, eating window, physical activity, and sleep. The mCC app is designed to run on Android and iOS devices and uses HIPAA compliant Amazon Web Server for server-side operations. A dedicated team of developers makes periodic updates to the app and to the backend server to comply with updates released by Apple, Google, and Amazon. The server side is designed to run multiple independent studies and the app is designed for individual customization. This allows study-specific customization by the investigator and user-specific customizations by participants.

For the TREMNIOS clinical trial, the mCC app was customized to be used in a single group assignment (TRE intervention group) study. After the enrollment of participants at Visit 2, the study investigator will generate a unique activation code. During the 2-week baseline period, participants will be asked to log their habitual food intake, physical activity, and sleep. Participants will not receive unsolicited feedback from the study investigators or the mCC app during baseline. At Visit 3, subjects will self-select a 10-h interval for consuming all of their food and beverages during the TRE intervention. Their chosen eating interval is highlighted in the app so that they can easily track the progress of their daily eating within their set interval. Participants will be asked to log all food intake, physical activity, and sleep quantity/quality every day for the baseline period and for the duration of the TRE intervention between Visits 3 and 7 (Figure 1). Other details regarding the use of the mCC app during the TRE intervention are included in Section 2.5.

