On the server-side, a sub-study dashboard was created for this clinical trial. In the study summary dashboard, the participant’s study code, and the date of activation of the app will be shown along with their daily logs in real-time. The designated members of the research team will have password-protected access to the real-time data, will log in to the dashboard at least twice weekly to monitor food intake data, and perform real-time tracking of TRE adherence, and follow up participants with inconsistent logging as necessary. If participants do not log or show inconsistent logging for two or more days, they will be contacted by telephone, and app users will be reinforced. Logging adherence will be determined by a minimum of two caloric entries >5 h apart for a given day. Adherence to the designated eating window implies that all caloric items were contained within a 15-min buffer on each side of the self-selected 10-h eating window. The time-stamped food data is also shown as a “feedogram” raster plot along with the eating duration for each day. This will offer a visual summary of the participant’s eating pattern. The protocol of this study has an app-based component allowing for real time tracking of adherence and correlating glucose levels with food intake.

The results from previous TRE studies which used mCC app [25,34,35] have demonstrated that adherence to mCC app use is high, mainly due to the simplicity of logging food metadata. The mCC app takes ~10 s for logging one meal by using the picture feature. If, for any reason, the participant does not wish to record a picture of food item(s), there will be also an option to enter the name of food in Polish or English (by choosing the name of food from the list) and the approximate time that food was consumed. Because a Polish version of mCC app is not available, we will provide participants with the list of common food with the names both in Polish and English. We will also provide the participants with required support regarding the use of mCC app, including special app training at Visits 1, 2, and 5. If a participant faces difficulty logging data or has questions about the app, he/she will be able to contact the study investigator through the feedback feature of the app. Although self-reporting of adherence by patients is generally not accurate, it was shown that the false-negative rate (i.e., food consumed but not logged) using the mCC app is ~10% [25,61].

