### 2.7. Primary and Secondary Outcome Measures

The primary and secondary outcome measures are depicted in Table 2. The adherence to TRE intervention is the primary outcome defined as the proportion of the total number of days recorded with mCC app during the TRE monitored intervention period (i.e., between Visit 3 and Visit 5) in which participants satisfied a requirement of a 10-h TRE eating window. The secondary outcome measures include changes in body weight, BMI, waist circumference, fat mass percentage, mean daily glucose levels obtained by CGM, mean fasting glucose levels obtained by CGM, FPG, lipids and HbA1c levels, HOMA-IR, as well as metabolic, neuroendocrine, inflammatory and oxidative stress biomarkers levels, eating window duration and timing of eating collected via mCC app and chrono-nutrition questionnaire, calorie intake collected via mCC app, physical activity and sleep duration collected via mCC app, systolic and diastolic BP, HR, and the health questionnaires scores. The main secondary outcome measures include changes in body weight and FPG between Visit 2 and Visit 5. The time frames for changes in all outcomes are indicated below in Table 2.

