Despite the encouraging results of previous TRE human studies, various aspects associated with an implementation of TRE in patients with diagnosed MetS require further clinical research which should be conducted exclusively in such populations of patients. Specifically, long-term feasibility of TRE intervention deserves further attention. In the pilot study of American population with MetS, the adherence to TRE and mCC app during a 12-week period was shown to be ~90 and ~85%, respectively [34]. In the study of diabetic patients, the rate of adherence varied greatly from 4% to 100% even over a relatively short period of 4-week TRE intervention [47]. This indicates that the adherence to TRE can be variable and is not always satisfactory. Wilkinson et al. [34] also observed that self-selecting of TRE eating window may be conducive to better adherence to TRE intervention. However, data on the extent to which MetS patients maintain a shortened daily eating window for an extended period of time during TRE intervention is lacking. The TREMNIOS trial is expected to provide insights into this question by evaluating the adherence of MetS patients to TRE over a relatively long period of 24 weeks. The TREMNIOS data characterizing the feasibility will aid in the design of a larger randomized controlled trial.

The impact of TRE on weight loss, decrease in body fat, energy restriction, decreasing appetite, and delimitation of eating window as well as the interactions between these TRE effects require elucidation. In addition, the effects of TRE on glycemic measures and lipid levels require further investigation as available data are limited and highly variable. Specifically, in several studies, no significant TRE-related improvements of some glucose or lipid measures were observed [34,35,36,37,38,39,40,43,45,46,47]. In addition, some findings suggest an increase in lipids post-early TRE or elevated FPG and morning glucose intolerance post-late TRE [37,41,53]. Moreover, TRE effects on metabolic, inflammatory, and oxidative stress biomarkers have been poorly investigated, so further evidence is needed regarding potential post-TRE improvements in oxidative stress, inflammation, and atherosclerosis [37,41,44,50,60]. In addition, more data on potential benefits of TRE on circadian-related metabolic and neuroendocrine biomarkers, BP, and daily rhythms of behavior such as eating window, meal timing, sleep, and physical activity would be desirable [63,64,65].

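### Adherence is said to be evaluated over 24 weeks, but the adherence proportion is defined only for the first 12, and the phases covered by the telephone follow-up are not stated

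*Protocol article*

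**What the plan says.** **Design.** Section 2.1 (Study Design) sets out "12 weeks of monitored intervention, and 12 weeks of self-directed intervention". Section 2.5 (TRE Intervention) places the first phase in the calendar, "participants will enter a 12-week monitored intervention between Weeks 3 and 15", and closes the second: "At Visit 7 (Week 27—intervention ends), participants will visit the clinic to remove the CGM".

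**The claim.** The Discussion notes that little is known about how far patients with metabolic syndrome keep to a shortened eating window over a long time. It says the trial will inform this by "evaluating the adherence of MetS patients to TRE over a relatively long period of 24 weeks".

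**The defined outcome.** Section 2.7 limits the adherence proportion to days recorded "during the TRE monitored intervention period (i.e., between Visit 3 and Visit 5". Sections 2.1 and 2.6.4 define it for the same phase, and Section 2.9 analyses it for that phase only, as a per-participant percentage reported as a group mean with standard deviation. In Table 2 adherence carries only the footnote for Visits 3 to 5.

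**What runs to Visit 7.** App logging continues to Visit 7 (Section 2.6.4), and Section 2.1 says compliance with TRE is assessed throughout the study. Table 2 lists eating window duration and timing of dietary intake with time frames that include Visits 5 to 7 and 3 to 7.

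**Contact with participants.** In Section 2.6.4, designated staff check the dashboard at least twice weekly and track adherence in real time. The rule continues: "If participants do not log or show inconsistent logging for two or more days, they will be contacted by telephone". No phase is named. For the self-directed phase, Section 2.5 says "no feedback from study investigators or push notifications from the mCC app will be provided to participants", and Section 2.1 says much the same. For baseline, Section 2.6.4 says: "Participants will not receive unsolicited feedback from the study investigators or the mCC app during baseline".

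**The concern.** The Discussion's claim and the outcome list do not match. The adherence figure that the plan will produce describes only the phase with education, prompts and staff support. A reader who expects a 24-week adherence figure will not find one defined. If one is produced later, its day rule and denominator could be chosen after the data are seen. This matters because the Discussion says the results will inform the length of the intervention and the use of the app in the planned randomised trial.

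The contact rules add a question of interpretation. If the telephone follow-up continues after Visit 5, the self-directed phase is not free of staff prompting. If it stops, logging may fall, and a proportion of recorded days would no longer be comparable between phases. As written, site staff cannot tell which is intended.

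**Working it through.** **1. The 24 weeks.** Inputs are the visit weeks in Section 2.5.
- Monitored phase: Week 15 − Week 3 = 12 weeks.
- Self-directed phase: Week 27 − Week 15 = 12 weeks.
- Total: Week 27 − Week 3 = 24 weeks. The stated figure reproduces.

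**2. Coverage of the adherence proportion.** Visits 3 to 5 are Weeks 3 to 15, so 12/24 weeks = (12 × 7)/(24 × 7) = 84/168 days = 50%.

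**3. Can eating window duration stand in for adherence after Visit 5?** Section 2.6.4 calls a day adherent when every caloric item falls inside the self-selected 10-h window, with a 15-min buffer on each side. Duration is the time from first to last caloric intake.
- *Position.* A day with 10 h of eating that starts 2 h after the chosen window opens, with the window not modified, has a compliant duration. It is not adherent, because 2 h exceeds the 15-min buffer.
- *Distribution.* The longest span that fits is 10 h + 2 × 15 min = 10.5 h. If every day is 11 h, the mean is 11 h and 0% of days are adherent. If 75% of days are 10 h inside the window and 25% are 14 h, the mean is 0.75 × 10 + 0.25 × 14 = 11 h and 75% of days are adherent. The same mean fits either proportion.

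The second point holds even if the day rule is read as duration alone.

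**4. What the monitored-phase figure can hide.** The Discussion reports about 90% adherence to TRE over 12 weeks in an earlier pilot in metabolic syndrome. Taking 90% for the monitored phase and **assumed** values for the self-directed phase, with equal weights, 24-week adherence is (90 + a)/2:

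| Assumed self-directed adherence a | 24-week adherence | Monitored-phase figure |
|---|---|---|
| 40% | 65% | 90% |
| 60% | 75% | 90% |
| 75% | 82.5% | 90% |
| 90% | 90% | 90% |

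**5. Why the number of logged days should accompany the proportion.** The denominator is days recorded. Hold the recorded-days proportion at 90% and vary logging. The 85% is the app adherence that the Discussion gives for the same pilot; 60% and 40% are assumptions. Days confirmed as adherent, as a share of all days, are then:
- 85% logged: 0.85 × 0.90 = 76.5%
- 60% logged: 0.60 × 0.90 = 54%
- 40% logged: 0.40 × 0.90 = 36%

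The reported proportion is 90% in all three cases.

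**6. The contact rules side by side.**

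| Phase | Feedback rule | Telephone follow-up for poor logging |
|---|---|---|
| Baseline | No unsolicited feedback (2.6.4) | Phase not stated |
| Monitored | Education, support and prompts (2.1, 2.5) | Natural reading: applies |
| Self-directed | No study-team feedback or app notifications (2.1, 2.5) | Phase not stated; logging is still required to Visit 7 (2.6.4) |

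The trigger for a call is missing or inconsistent logging, not eating outside the window. Feedback is not defined.

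**The case against.** The strongest reply is that the Discussion's question is how far patients maintain a shortened window, and that eating window duration and timing, both prespecified to Visit 7, speak to it. Retention to the final measures is also a feasibility measure. This stands in part. A reader might infer that half of the 24 weeks goes unanswered, but the documents do not support that: persistence is measured in part, and the missing proportion can be computed from data already planned. It does not dispose of the point. The sentence promises adherence, the plan gives adherence its own definition, and step 3 shows that duration does not recover it.

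On contact, a reader might infer that the telephone rule and the no-feedback rules cannot both be followed. That goes too far. A reminder to log can coexist with no feedback on eating, and the phase-specific rules can be read as limiting the general one. Section 2.6.4 also schedules app training at Visit 5, so some logging support at the start of the self-directed phase is foreseen. What stands is that the scope is not stated.

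A reader might also take testing persistence without support to be the declared purpose of the second phase. The documents give no such reason; the Discussion speaks of the length of the period.

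Finally, an article condenses a fuller protocol, which may settle the calls. That softens the second part. It does not touch the first, because the article itself repeatedly states the limit to Visits 3 to 5.

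**Conclusion.** The point holds in a limited form. The plan says adherence will be evaluated over 24 weeks but defines and analyses the adherence proportion for only 12 of them (84 of 168 days). Eating window duration and timing cover the rest in part, but they cannot replace the proportion. This conclusion rests only on the visit weeks and on the definitions in Section 2.6.4; the figures in steps 4 and 5 illustrate it and depend on the assumptions stated there.

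The scope of the telephone follow-up outside the monitored phase is unreconciled with the feedback rules, not in flat contradiction with them. Neither matter affects the primary outcome, which ends at Visit 5. Both are worth settling because the self-directed data are meant to inform the next trial.

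**What to change.** 1. Add to Table 2, as a secondary outcome, the adherence proportion for Visits 5 to 7. Use the same day rule and app data as for Visits 3 to 5, and report the within-participant change between the two phases.
2. Report the number of days logged in each phase beside each proportion.
3. If item 1 is not wanted, reword the Discussion so that it claims adherence over the 12 monitored weeks and eating window duration and timing to Visit 7.
4. Reconcile Sections 2.1, 2.5 and 2.6.4 by stating whether the adherence tracking and telephone follow-up apply at baseline and in the self-directed phase. If calls are made outside the monitored phase, report their number.

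The cost is some wording and one more analysis of data already collected. If calls are confined to the monitored phase, there may be more unlogged days after Visit 5, which item 2 would make visible.
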